**1. Rationale & background information**

Chronic lower back pain is associated with high morbidity worldwide, and a report suggests that more than half the world population experiences lower back pain at least once in their lifetime. Many patients with non-specific chronic lower back pain are not indicated for surgical procedure and are treated by conservative therapy. To date, sufficiently satisfactory approaches to treat lower back pain have not been determined. The Arthrokinematic Approach-Hakata (AKA-H) method is an approach uniquely developed in Japan to manually treat abnormal intracapsular movement. The aim of this study was to demonstrate that this approach can be an effective therapy for non-specific chronic lower back pain.

**2. Study goal and objective**

**Study goal and objective:** To determine the effectiveness of AKA-H method for chronic lower back pain.

**3. Study Design**

・Using a random number table created by free-software R (http://www.r-project.org), the patients were randomly assigned to the AKA-H (AKA-H) or the sham (S) groups.

・This study was a parallel group comparison in which the AKA-H group and S group were compared for 6 months. The study was randomized at the level of the individual patient, and it was a single-blind RCT in which only the patients were blinded to the details.

**4. Methodology**

**・Patient selection criteria**

The subjects of this study were individuals who met all of the following inclusion criteria and for whom none of the following exclusion criteria apply.

**Inclusion Criteria:**

・Non-specific lower back pain lasting for at least the previous 6 months

・The patient received conservative orthopedic treatment from an orthopedic physician or another physician but had shown no improvement in symptoms

・The patients’ age was between 18–79 years.

**Exclusion Criteria:**

- History of spinal operations within the 6 months before the trial.
- Current history of infection, neoplasm, metastasis, osteoporosis, rheumatoid arthritis, fracture, or radicular syndrome
- Pregnancy

**Sampling and Recruitment**

AKA-H has been widely known among patients in Japan through mass communication or personal communication and is expected to be referred from home doctors. A list of hospitals where AKA-H is available is shown on the website of the Japanese Medical Society of Arthrokinematic Approach(http://www.aka-japan.gr.jp). Doctors listed there are specialists or advising doctors who have passed an exam stipulated by the Society. When patient desires treatment by AKA-H, he/she will be required to call Saitama Prefectural Rehabilitation Center first, and will be asked his/her address, phone number, and age by a Center staff. Then, the first author will contact him/her by phone within 3 days to give a full explanation of the RCT. If the patient shows his/her willingness to participate in the study, he/she will receive an email with instructions on the AKA-H procedure, consent form, treatment flow at the first visit, specially created calendar type form to record VAS scores, and a scale to measure VAS.

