**・Randomization**

Output 0 or 1 in order using a random number table created free-software R (for example, 0 for the first person, 1 for the second person, and 1 for the third person). A piece of paper with 0 on it is enclosed in an envelope with 1 on it, and the envelope is sealed. A piece of paper with 1 on it is enclosed in an envelope with 2 on it, and then the envelope is sealed. This procedure will be done by a nurse in the outpatient department. The nurse will keep and store the envelopes without being informed of the purpose of creating those envelopes so that the first author cannot be involved in the randomization. At the patient’s first visit, a nurse will bring an envelope with the number corresponding to the patient number to the first author after the patient walks in the outpatient medical examination room. Then, the first author opens the envelope to provide sham procedure or AKA-H after confirmation of the number without informing the patient. Caution is needed to have the patient not recognize which procedure will be performed.

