**Interventions**

The patients are randomized to receive the AKA-H method or the sham technique. The AKA-H method is applied once a month for 6 months to the sacroiliac joint for treatment of low back pain using the following techniques: 1) upward gliding, 2) downward gliding, 3) superior distraction, and 4) inferior distraction.

- **Sham technique:** During the sham technique, the patient lies sideways with both hips and knees extended (each joint is close-packed), and the therapist stands on the ventral side of the patient. The therapist’s thumb, on the cephalic side of the patient, is placed on the S1 spinous tubercle, giving a light downward force while the index finger of the therapist’s other hand is placed underneath the S1 spinous tubercle to counteract the downward force; thus, the sacroiliac joints do not actually move. The same procedure is performed in which the therapist’s thumb, on the caudal side of the patient, is placed on the S3 spinous tubercle with the index finger of the therapist’s other hand underneath it. This procedure is slowly repeated twice with the procedure on S1 first, followed by S3, alternately.

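### Earlier AKA-H is not an exclusion and callers who want AKA-H are emailed its instructions, so some patients could recognise the sham and weaken the trial's only blinding

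*Protocol*

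**What the plan says.** Protocol section 3 (Study Design) sets the blinding: "it was a single-blind RCT in which only the patients were blinded to the details". Section 5 makes the primary outcome a monthly mean of daily VAS scores that patients record themselves. The secondary outcomes, RDQ and SF-36, are questionnaires that patients complete.

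Under Sampling and Recruitment in section 4, the source population is people who already want the active treatment: "When patient desires treatment by AKA-H, he/she will be required to call Saitama Prefectural Rehabilitation Center first". The same paragraph says that "AKA-H has been widely known among patients in Japan through mass communication or personal communication", and refers to a public list of hospitals offering it. Once a caller is willing to take part, "he/she will receive an email with instructions on the AKA-H procedure, consent form, treatment flow at the first visit". The envelope is opened only at the first visit, so this email precedes allocation.

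The eligibility lists deal with earlier treatment in two places. The inclusion criterion reads: "The patient received conservative orthopedic treatment from an orthopedic physician or another physician but had shown no improvement in symptoms". The exclusion reads: "History of spinal operations within the 6 months before the trial". Neither mentions AKA-H.

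Under Interventions, AKA-H consists of "1) upward gliding, 2) downward gliding, 3) superior distraction, and 4) inferior distraction". The sham is a light, counteracted pressure on the sacrum, arranged so that the sacroiliac joints stay still. Under Randomization, the first author opens the envelope, does not tell the patient the result, and gives the procedure. The protocol adds: "Caution is needed to have the patient not recognize which procedure will be performed".

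**The concern.** With no blinded assessor and no objective endpoint, the comparison rests on patients not knowing which procedure they received. Recruitment and eligibility work against that in two ways. A patient who has already had AKA-H can be randomised to a procedure that differs from it physically, and would meet it at each monthly visit for six months. A patient who has been sent a detailed account of AKA-H may also notice that what is done does not match.

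Patients who came for AKA-H and conclude that they are getting something else have a plain reason to report less improvement. They may also ask for disclosure and a change to AKA-H, which the section on change criteria allows. Either way, part of the observed difference, or of its absence, would reflect what patients believed.

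**Working it through.** The protocol gives no sample size, SD, target difference or expected rate of recognition, so there is no figure to reproduce. The check is first of the text and then of what an assumed rate of recognition would do.

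**Text, side by side**

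1. *Can a patient with AKA-H experience enter?* Yes. The inclusion criterion asks for unsuccessful conservative treatment from an orthopedic or other physician and does not require patients to be AKA-H-naive. The only excluded earlier treatment is recent spinal surgery.
2. *Does such a patient have a basis for recognising the sham?* Yes, by feel. AKA-H glides and distracts the sacroiliac joint, whereas the sham is built to prevent that movement. The protocol does not describe the patient's position or the hand placement for AKA-H, so a difference in appearance cannot be established.
3. *Does the email add to this?* Possibly. It concerns the AKA-H procedure and goes out before allocation. Its content is not shown, so the detail it gives is unknown.
4. *Would recognition reach the outcomes?* Yes. All the named outcomes are patient-reported.

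**Illustration on assumed inputs**

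Let *q* be the share of sham patients who recognise the sham, and *b* the amount, in SD, by which they then score worse. With no true effect and no switching, the spurious difference is *d* = *q* × *b*. For *n* per arm, SE = √(2/*n*) in SD units. The chance that a two-sided 5% normal test rejects is Φ(*d*/SE − 1.96) + Φ(−*d*/SE − 1.96).

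Worked case with *q* = 0.25, *b* = 0.5, *n* = 60: *d* = 0.125, SE = √(2/60) = 0.183, *d*/SE = 0.685. The probability is Φ(−1.275) + Φ(−2.645) = 0.101 + 0.004 = 0.105.

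| q | b (SD) | d (SD) | n = 30 | n = 60 | n = 90 |
|---|---|---|---|---|---|
| 10% | 0.25 | 0.025 | 5.1% | 5.2% | 5.3% |
| 25% | 0.5 | 0.125 | 7.7% | 10.5% | 13.4% |
| 50% | 0.5 | 0.25 | 16.2% | 27.8% | 38.9% |

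*q*, *b* and *n* are all assumptions. The calculation compares two means at one time point and is not the planned repeated measures analysis.

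**Adding the switch**

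Let *s* be the share of sham patients who change to AKA-H, and *g* the improvement they report because of the change. Under the intention-to-treat principle in section 6 they stay in the sham arm, so the net bias becomes *q* × *b* − *s* × *g*. It is positive, in favour of AKA-H, when *q* × *b* exceeds *s* × *g*, and negative when it is smaller. If everyone who recognises the sham switches (*s* = *q*), the sign is that of *b* − *g*. The protocol fixes none of the four quantities.

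**The case against.** The protocol does take blinding seriously. Allocation is in a sealed envelope brought in after the patient has entered the room. The patient is not told the result. The sham is a hands-on procedure on the sacrum, and routine disclosure waits until the end. A reader might infer that the caution is the only safeguard, but these measures show otherwise.

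A reader might also infer that the sham looks different from AKA-H. The protocol does not support that. AKA-H positioning is not described, and in the sham the patient lies on one side with the contact on the sacrum, behind the body. Only the difference in joint movement can be taken from the text.

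The scale of earlier exposure is open. Being widely known is not the same as having been treated, and Safety Considerations says that few facilities use the method. Wanting AKA-H does not make a patient able to recognise it, and before allocation that wish is balanced between the arms by randomisation. The email may be general in content.

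Finally, a reader might infer that the bias must favour AKA-H. Recognition alone probably would push that way, but switching under intention-to-treat could narrow the difference.

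All of this stands, and it limits the point to a risk of unknown size. It does not remove the gap: the listed safeguards conceal the assignment, but none keeps out a patient who already knows how AKA-H feels.

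**Conclusion.** The point holds as a design weakness that should be corrected. Followed as written, the protocol can randomise a patient with AKA-H experience to a sham that the patient has a direct basis for recognising, in a trial where patient belief is the only thing blinded and every outcome is self-reported. This part rests on the eligibility lists and the description of the two procedures, and does not depend on the email. The part about the email is conditional on content that is not shown.

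The size cannot be derived. In the illustration the effect on the false-positive rate runs from negligible (5.1%) to serious (38.9%), entirely according to the assumed inputs. The net sign is also undetermined once switching is allowed for. The protocol does not support saying that sham patients will recognise the sham, that the result is biased towards AKA-H, or that the bias is any particular number of millimetres.

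**What to change.** Two changes in section 4 of the protocol:

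- Under Exclusion Criteria, add *any previous AKA-H treatment*.
- Under Sampling and Recruitment, replace the emailed AKA-H instructions with a description that fits both procedures equally well.

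Optionally, ask each patient to guess the treatment after the first session and again before the disclosure described under Post-Treatment Therapy, and report the answers by arm. This does not prevent unblinding, but it would let a reader judge how far it went.

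The cost is one line of eligibility, a reworded email and, if adopted, one question on an existing form. The drawback is a somewhat smaller recruitment pool. If that loss is not acceptable, or patients are already enrolled, the fallback is to record earlier AKA-H and run a sensitivity analysis by it. These changes leave the treatments, their schedule and the switching rule as they are.

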**・Randomization**

Output 0 or 1 in order using a random number table created free-software R (for example, 0 for the first person, 1 for the second person, and 1 for the third person). A piece of paper with 0 on it is enclosed in an envelope with 1 on it, and the envelope is sealed. A piece of paper with 1 on it is enclosed in an envelope with 2 on it, and then the envelope is sealed. This procedure will be done by a nurse in the outpatient department. The nurse will keep and store the envelopes without being informed of the purpose of creating those envelopes so that the first author cannot be involved in the randomization. At the patient’s first visit, a nurse will bring an envelope with the number corresponding to the patient number to the first author after the patient walks in the outpatient medical examination room. Then, the first author opens the envelope to provide sham procedure or AKA-H after confirmation of the number without informing the patient. Caution is needed to have the patient not recognize which procedure will be performed.

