**Treatment schedules**

**Duration and Frequency**

- Patients will be treated only as outpatients.
- Outpatient treatment shall be once a month for six months, with evaluation in the seventh month.
- In principle, the oral medication will be continued.

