**5. Outcomes and Confidentiality**

Primary outcome and secondary outcomes

- Primary outcome is mean VAS score over a month from the previous visit.
- Participants are required to record their VAS score in a form every day at almost the same time for at least 1 month until the first visit and bring the recorded form along with consent form at the first visit.
- Secondary outcomes are Roland-Morris Disability Questionnaire (RDQ) and 36-Item Short-Form Health Survey (SF-36).
- Participants will fill RDQ and SF-36 at every visit including the first visit at the waiting room by advance reservation only before seeing a doctor. Participants are required to visit the outpatient office once a month, in principle, for 6 months after initiation of treatment.
- A VAS record form will be collected at every visit, and a new one will be provided to the participants.
- RDQ and SF−36 will be filled at the waiting room and will be collected at every visit. Those collected record forms will be stored in the locked locker at outpatient department.

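### The only named operator knows the arm and gives both procedures, and no rule equalises encouragement or contact time between AKA-H and sham

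*Protocol*

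**What the plan says.** Section 3 (Study Design) declares that "it was a single-blind RCT in which only the patients were blinded to the details". The Randomization paragraph of section 4 says who learns the allocation: "At the patient’s first visit, a nurse will bring an envelope with the number corresponding to the patient number to the first author", after which "the first author opens the envelope to provide sham procedure or AKA-H after confirmation of the number without informing the patient". The next sentence is the protocol's only instruction on conduct during delivery: "Caution is needed to have the patient not recognize which procedure will be performed".

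Duration and Frequency sets the contacts: "Outpatient treatment shall be once a month for six months, with evaluation in the seventh month". No section names the operator for the later visits; Interventions refers only to a therapist.

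Interventions describes the sham in detail: patient position, hand placement, direction of force, order, and two repetitions. AKA-H is given as a list of techniques for the sacroiliac joint, "1) upward gliding, 2) downward gliding, 3) superior distraction, and 4) inferior distraction", with no position, repetitions or duration.

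Section 5 makes mean VAS over the month since the previous visit the primary outcome, recorded by the patient on a form, with RDQ and SF-36 as secondary outcomes. On their timing it says: "Participants will fill RDQ and SF-36 at every visit including the first visit at the waiting room by advance reservation only before seeing a doctor". Forms are collected at every visit and kept in a locked locker, but the section does not say who collects them.

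**The concern.** An operator of a manual technique cannot be blinded, so a sham-controlled comparison depends on the two arms receiving the same attention, time and expectation apart from the technique itself. The protocol sets a goal for this (the patient should not recognise the procedure) but no means, and the goal is narrower than what is needed. A patient may have no idea which procedure was given and still receive warmer reassurance, a longer session or a remark that the joint is moving better.

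VAS, RDQ and SF-36 all respond to such differences. The likely direction is towards AKA-H, because section 1 gives the aim as showing that the method can be effective. The operator's manner could also affect whether a sham patient stays in the assigned arm, since the Change criteria let a patient ask for disclosure and move to AKA-H. The analysis in section 6 compares the arms as treated by this process. A repeated measures ANOVA cannot separate the effect of the consultation from the effect of the technique.

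**Working it through.** No figure in the protocol bears on this point: it gives no sample size, SD, effect size, alpha or power. The check is therefore mainly a comparison of the text, followed by an illustration on assumed inputs.

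**What each existing measure covers**

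| Measure | Where | Protects | Controls operator's manner or contact time? |
|---|---|---|---|
| Sealed envelopes held by a nurse, brought after the patient has entered the room | Randomization | Allocation | No |
| Sham with set position, hands and repetitions | Interventions | Credibility of the sham | No; no matching specification for AKA-H |
| Patient-kept VAS form | Section 5 | Rating away from the operator | No; ratings follow the contact |
| RDQ and SF-36 before the doctor is seen | Section 5 | The moment of rating | No; earlier contacts have already acted |
| Caution sentence | Randomization | Recognition of the procedure | No; no method, and a different target |

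**Exposure.** One treatment contact a month for six months gives 1 × 6 = 6 planned contacts per patient. The document places the first author, with the arm known, at the first. For the other five it names nobody.

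**Specification of the two arms.** Sham: position, hand placement and two repetitions. AKA-H: four named techniques only. Equal contact time cannot be inferred from the text.

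**Illustration (all inputs assumed).** Let the true AKA-H effect be 0, the non-specific difference be b in SD units, n patients per arm, two-sided alpha 0.05, and a simple two-group comparison in place of the planned repeated measures analysis.

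SE = √(2/n)

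P(significant) = Φ(b/SE − 1.96) + Φ(−b/SE − 1.96)

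Worked case, n = 50 and b = 0.2: SE = √(2/50) = 0.20, so b/SE = 1.00, and P = Φ(−0.96) + Φ(−2.96) = 0.170.

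| n per arm | b = 0 | 0.1 | 0.2 | 0.3 | 0.5 |
|---|---|---|---|---|---|
| 30 | 5.0% | 6.7% | 12.1% | 21.3% | 49.1% |
| 50 | 5.0% | 7.9% | 17.0% | 32.3% | 70.5% |
| 75 | 5.0% | 9.4% | 23.2% | 45.1% | 86.5% |
| 100 | 5.0% | 10.9% | 29.3% | 56.4% | 94.2% |

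Across each row the error rate grows with the bias; down each column with b above 0 it grows with the sample. Recruiting more patients does not protect against this bias. The table says nothing about whether b is near 0 or near 0.5 in this trial.

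**The case against.** The strongest reply is that the limitation is inherent and openly declared: the trial is described as single-blind, and nobody can blind the hands that give a manual treatment. Naming one person for both procedures also has a benefit, since it avoids confounding arm with therapist skill. This stands. The point is not that the operator is unblinded, but that nothing is done about what follows from it.

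A reader might infer more than the text supports, in five ways.

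- *One operator at every visit.* The protocol places the first author at the first visit only. Continuity is a reasonable guess, not a statement.
- *Caution is the only safeguard.* This is not so for the trial as a whole, as the first table shows. It is true only of operator conduct during delivery.
- *The recruitment call adds to the bias.* Under Sampling and Recruitment, "the first author will contact him/her by phone within 3 days to give a full explanation of the RCT", but that call comes before the envelope is opened and so cannot differ by arm.
- *Extra effort is pure bias.* More manual effort in the AKA-H arm is partly more AKA-H. Only unequal encouragement, attention and time outside the technique are non-specific.
- *The operator adjusts to the monthly scores.* The protocol does not say that the operator reads the forms before treating. It leaves this open.

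It may also be said that a missing script is a request for more detail. But the protocol does address operator conduct, and does so with a sentence aimed at a different problem. Conduct at the visit is a protocol matter that a statistical analysis plan would not settle.

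**Conclusion.** The point holds in a limited form. The only named operator knows the arm, all outcomes are patient-reported, and no provision equalises encouragement or contact time. Part of any VAS difference could therefore be non-specific, most plausibly in favour of AKA-H.

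The size cannot be derived from the protocol, and no shift in millimetres should be attached to it. The percentages above depend wholly on assumed biases and sample sizes. They show only that a modest bias would matter and that a larger sample would not remove it. It would be wrong to conclude that the trial's blinding fails or that a positive result must be an artefact; the document supports neither. This is an inexpensive improvement worth making, not a fatal flaw.

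**What to change.** - **Randomization and Interventions (section 4).** Replace the caution sentence with a rule for both arms at every visit: the same written script, the same planned contact time, and no comment to the patient on joint findings or expected benefit. State who treats at each visit. The rule governs communication and time, not the content of either technique, and must not limit what has to be said for safety.
- **Section 5.** Have the outpatient nurse collect the VAS form together with RDQ and SF-36 before the consultation and place them in the existing locker. This must not bar the physician from information needed for safety, for the decisions under Change criteria, or for those under Possible Adverse Events.
- **Final evaluation.** Before the disclosure described under Post-Treatment Therapy, ask each patient to guess the arm, and record who had already been told. Interpret the guesses with care, since improvement itself can lead a patient to guess AKA-H.

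The cost is a one-page script, a change in who handles existing forms, one extra question, and slightly less natural consultations.
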